### Sample size

The sample size was calculated statistically to obtain a power of 80% with an alpha error of 0.05. In order to demonstrate an effect in calcium and vitamin D treated patients, consisting of a 30% to 20% reduction in the incidence of falls (relative risk reduction equivalent to 33%), a sample size of 586 (293 in the treatment group and 293 in the non-treatment group) is needed. Assuming a 20% loss to follow-up, 704 subjects between the two groups need to be selected. The two groups will be of equal size in order to obtain the greatest statistical power.

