**Methods/Design:**

Phase III, randomized, double blind, placebo-controlled trial to evaluate the efficacy of already marketed drugs in a new indication. It will be performed at Primary Care doctor visits at several Healthcare Centers in different Spanish Health Areas. A total of 704 non-institutionalized subjects aged 65 years or older will be studied (sample size calculated for a statistical power of 80%, alpha error 0.05, annual incidence of falls 30% and expected reduction of 30% to 20% and expected loss to follow up of 20%). The test drug containing 800 IU of vitamin D and 1000 mg of calcium will be administered daily. The control group will receive a placebo. The subjects will be followed up over two years. The primary variable will be the incidence of spontaneous falls. The secondary variables will include: consequences of the falls (fractures, need for hospitalization), change in calcidiol plasma levels and other analytical determinations (transaminases, PTH, calcium/phosphorous, albumin, creatinine, etc.), change in bone mass by densitometry, change in muscle strength in the dominant hand and change in musculoskeletal strength, risk factors for falls, treatment compliance, adverse effects and socio-demographic data.

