### Statistical analysis

After performing data cleaning and imputation, exploratory analysis and categorization or transformation of variables the following analyses will be performed:

- Comparison of the variables of interest and the stratification and potentially confounding variables in the treated and non treated groups at the start of the study. We will determine if, despite using randomized assignment, the two groups are homogenous.

- A first raw analysis will be performed to calculate the following parameters and their confidence intervals: ARR (absolute risk reduction), RRR (relative risk reduction) and NNT (number necessary to treat). A stratified analysis will also be performed adjusting for each independent variable. If there are differences between the raw RR and the adjusted RR, the homogeneity between the categories will be determined to establish if the variable is effect modifying or confounding. The incidence of the variables in each group will be described and compared (comparison of proportions by the chi-squared test).

- A survival (fall-free period) analysis will be performed in both study groups (Kaplan-Meier and Log Rank test). Then the effect of treatment on the risk of falls will be determined by constructing a Cox proportional hazards model.

- The effect of treatment on calcium and vitamin D levels will be estimated adjusted for changes in treatment compliance (generalized linear models for repeated measures).

Data will be analyzed on an intention to treat basis including all randomized patients in the efficacy and safety analyses according to their randomized treatment group regardless of the treatment received. A per protocol analysis will also be performed for the primary variables. This will exclude patients who did not meet any of the selection criteria and did not comply with treatment.

For ethical reasons an intermediate analysis will be performed to decide if the study should be discontinued prematurely because of frequent adverse effects occur or an obvious improvement in the test group.

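### The 20% loss allowance was applied by multiplying by 1.2 rather than dividing by 0.8, so 704 subjects leave about 563 after that loss, not the 586 required

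*Protocol article*

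**What the plan says.** The Sample size section sets out the calculation in two steps.

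- **Before attrition.** The targets are given as "The sample size was calculated statistically to obtain a power of 80% with an alpha error of 0.05". The effect is described as "consisting of a 30% to 20% reduction in the incidence of falls (relative risk reduction equivalent to 33"%, and the result is "a sample size of 586 (293 in the treatment group and 293 in the non-treatment group) is needed".
- **After attrition.** "Assuming a 20% loss to follow-up, 704 subjects between the two groups need to be selected". Allocation is equal: "The two groups will be of equal size in order to obtain the greatest statistical power".

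The Methods/Design paragraph of the abstract repeats the total of 704, the 80% power and an "expected loss to follow up of 20"%. The Statistical analysis section names the matching test, "comparison of proportions by the chi-squared test". Nowhere does the article define the 20% in another way or give a different rule for the allowance.

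**The concern.** An allowance for loss should be set so that the subjects who remain are as many as the power calculation requires. People are lost from the group that enters, so the required number is divided by the proportion retained. Going from 586 to 704 adds 20% of the smaller, post-loss number, which is not the same as allowing for 20% of those who enter.

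The figure matters because 704 is the recruitment target and 80% power is its justification. The calculation has no slack: at 293 per arm the power is 79.98%, so any shortfall takes it below the stated level. The article treats attrition as a real risk. Its Discussion raises the possibility of differential loss between groups and gives the length of the study as one reason.

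**Working it through.** **Inputs**

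| Input | Value | Source |
|---|---|---|
| Control and treated proportions | 0.30 and 0.20 | Sample size section |
| Alpha | 0.05; two-sided assumed | Sample size section; sidedness not stated |
| Power | 80% | Sample size section; abstract |
| Evaluable subjects needed | 586 (293 per arm) | Sample size section |
| Loss to follow-up | 20%, read as a share of those entered | Sample size section; abstract |
| Total after allowance | 704 | Sample size section; abstract |

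**Step 1: reproduce 293 per arm.** Use the pooled two-proportion formula without continuity correction, with mean proportion p̄ = 0.25:

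n = [z(0.975)·√(2p̄(1 − p̄)) + z(0.80)·√(p₁(1 − p₁) + p₂(1 − p₂))]² / (p₁ − p₂)²

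= [1.960 × √0.375 + 0.8416 × √0.37]² / 0.01 = 293.15

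This matches the stated 293 (strict rounding up would give 294). A one-sided test would need only 231 per arm, so the plan must have used a two-sided 0.05. The base of 586 is sound.

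**Step 2: reproduce 704.**

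- Multiplying: 586 × 1.2 = 703.2. By arm, 293 × 1.2 = 351.6, rounded up to 352, and 2 × 352 = 704. This is the stated figure.
- Dividing: 586 / 0.8 = 732.5. By arm, 293 / 0.8 = 366.25, rounded up to 367, and 2 × 367 = 734.

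Only multiplication gives 704. The choice of base formula does not explain the gap. Even the smallest two-sided variant (unpooled variance, 290.4, so 291 per arm) gives 2 × 364 = 728 when divided by 0.8.

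**Step 3: what 704 delivers.**

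- Evaluable after 20% loss: 704 × 0.8 = 563.2, or about 281.6 per arm.
- Shortfall in evaluable subjects: 586 − 563 = 23.
- Shortfall in entered subjects: 734 − 704 = 30, and 30 / 734 is about 4%.
- Largest loss that still leaves 586: 1 − 586/704 = 16.8%.

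**Step 4: power.**

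Power = Φ{[(p₁ − p₂)√n − z(0.975)·√(2p̄(1 − p̄))] / √(p₁(1 − p₁) + p₂(1 − p₂))}

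| Evaluable per arm | Power |
|---|---|
| 293 (586 in total) | 80.0% |
| 281.6 (704 less 20%) | 78.4% |
| 281 (whole subjects) | 78.3% |

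The loss is about 1.6 percentage points.

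**The case against.** Nobody disputes the arithmetic. The case on the other side is about how much it matters.

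- **The effect is small.** A fall of 1.6 points in power will not decide the trial, and the 20% is a round assumption with no source given. This stands as a statement of size. It does not make the figures agree, and 704 against 734 is more than rounding.
- **Lost subjects may still contribute.** The Statistical analysis section plans an intention-to-treat analysis of everyone randomised, mentions imputation, and adds Kaplan-Meier, log-rank and Cox analyses. Falls are recorded every three months, so a fall before loss would count. If all 704 counted fully, nominal power would be 86.7%; that is an upper bound, because imputation does not restore full information. So the 78% applies when lost subjects contribute no outcome data. But inflating for loss is the plan's own choice, and it treats those subjects as not counting towards the 586.
- **Time base.** The abstract gives 30% as an annual incidence, while follow-up lasts two years. If annual risks were constant and independent (an assumption the article does not make), the two-year proportions would be 1 − 0.7² = 51% and 1 − 0.8² = 36%. Power at 281 per arm would then be about 95%. This is a fair sensitivity case, but the plan powers the trial on 30% versus 20%, and the allowance has to be checked against those rates.
- **The 20% might mean 20% of 586.** Nothing in the article says so. On that reading the expected loss among those entered is (704 − 586)/704 = 16.8%, and calling it a 20% loss to follow-up is itself wrong.

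**Conclusion.** The concern holds: the sample size is wrong as written. The stated 704 does not provide the stated 586 under the stated 20% loss. It leaves about 563, with power of about 78% instead of 80%. The discrepancy is 30 entered subjects (about 4%), 23 evaluable subjects and about 1.6 points of power. It does not threaten the trial, but it affects the recruitment target and its justification, and it is printed twice.

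The inconsistency in the count rests only on reading the 20% as a share of the 704. The article says these subjects are to be selected (Sample size) or studied (abstract); they are taken here as the number randomised. The power figure also assumes a two-sided 0.05, the plan's 30% versus 20%, and no outcome data from subjects lost.

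**What to change.** Correct the Sample size section and the Methods/Design paragraph of the abstract together, in one of three ways:

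1. Keep 704 and 20%, and restate the power: 704 randomised gives about 563 evaluable after 20% loss and power of about 78% for 30% versus 20%, if lost subjects contribute no outcome data.
2. Keep 704 and 80%, and restate the allowance: 80% power holds for loss to follow-up of up to 16.8%.
3. Keep both 80% and 20%, and change the total to 734 (367 per arm).

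The first two cost one sentence in each place and no extra subjects; the stated power or the tolerated loss becomes slightly less favourable. The third needs 30 more subjects. In each case, state that the test is two-sided and that the loss is a proportion of those randomised.

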### Blinding and group assignment

After determining that the patients meet the inclusion criteria and do not meet the exclusion criteria, they will be randomized and assigned to the treatment or the control group. The randomization list will be generated by a computer using pseudo-random numbers. Randomization will be centralized. The investigators will receive the information necessary to give each patient the corresponding treatment in blinded conditions. To protect the blinding, the placebo and the test treatment will look exactly the same. The randomization list will contain a patient identification number and the number of the treatment to which he/she has been assigned. This patient number will be used as patient identification in all trial documentation, including the case report form.

To ensure objectivity in measuring the results, the study will be performed in blinded conditions for the patients, the investigators and the data analysts who will not know the labels of the groups they will compare. The placebo and test treatment will have an identical appearance and will only be identified by a code number. The assignment will be unknown by the patient and investigator.

### Intervention

The pharmacological intervention will be the daily administration of chewable tablets containing 800 IU of vitamin D and 1200 mg of calcium. They will be administered over 2 years during the months of November to April in order to avoid the influence of sunlight. Dose adjustment is not contemplated during the study. Concomitant treatment with thiazide diuretics, digitalis drugs, anticonvulsants or barbiturates will not be permitted.

The control drug will be chewable placebo tablets with the same appearance as the test drug.

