### Study location and subjects

Patients will be recruited at primary care doctor visits. The subsequent visits will be at the health Centers of the participating Spanish autonomous communities: Castille-La Mancha, Andalusia, the Balearic Islands and Catalonia.

The target population is non-institutionalized patients of 65 years or over. The inclusion criteria are: aged over 65 years with normal renal function, normal transaminase levels, normal calcium blood levels, not homebound (not immobilized) nor in socio-healthcare institutions. The exclusion criteria are: need for medical treatment with calcium or vitamin D, hypersensitivity to or contraindication for calcium or vitamin D, medical treatment that includes calcium or vitamin D, physical disability that impedes their collaboration, taking thiazide diuretics, oral anticoagulants, hormone replacement therapy, digitalis drugs, anticonvulsants or barbiturates and having any of the following diseases: lithiasis, renal impairment (serum creatinine > 1.4 mg/dl), hypo or hyperthyroidism, Paget's disease, chronic liver disease, tumors, sarcoidosis, impaired intestinal absorption or chronic alcoholism (> 40 g/day).

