### Subject follow-up

The subjects will be followed up for a 2 year period. They will be selected at primary care doctor visits, when they will be asked to participate in the study. Once the patients have given their informed consent they will be given an appointment for the randomization visit and an appointment for the analytical tests and densitometry examination before starting treatment.

At the randomization visit the patient will be assigned to one of the study groups, their medical history will be taken, they will be given a physical examination and the study medicine will be dispensed. The following visits will be at 3, 6, 9, 12, 15, 18, 21 and 24 months. At these visits the efficacy (data on falls, fractures, muscle strength and mobility and musculoskeletal function) and safety (the detection of adverse effects) parameters will be collected, treatment compliance will be evaluated and the medication will be dispensed.

Discontinuation of treatment will be for the following reasons: completion of follow-up period (two consecutive years), death, violation of protocol, adverse event, inter-current illness causing immobilization for more than 30 days and patient abandoning trial or withdrawing informed consent.

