### Definitions of the primary variables and measuring methods

The primary variable will be the incidence of spontaneous falls according to the FICSIT (Frailty and Injury: Cooperative Study of Intervention Techniques) definition: "Unintentionally coming to rest on the ground, floor, or other lower level. Coming to rest against furniture or a wall was not counted as a fall." Information on the circumstances of the fall (apparent cause, activity performed, time and place and need of help) will be obtained by an interview.

The following are the secondary variables:

- Consequence of falls (bone fractures at any location, need for healthcare, need for hospitalization, bed-ridden).

- Change in calcidiol [25(OH)D3] plasma levels (determined by RIA at baseline and at 6 and 18 months). Vitamin D deficiency is defined as a calcidiol plasma level lower than 10 ng/ml.

- Levels of transaminases, parathyroid hormone (PTH), calcium, phosphorous and serum creatinine, determined by tests on venous blood samples obtained in a fasted state. Calcium/creatinine index, determined by analysis of second morning urine.

- Change in bone mass (bone density or mineral content) obtained by densitometry (risk of fracture). Osteoporosis will be diagnosed based on a densitometry T-score of less than 2.5 in the vertebral column, according to WHO criteria.

- Change in muscle strength in the dominant hand. Determined by dyanometry (with a mean of 3 attempts to obtain a muscle strength measurement).

- Changes in musculoskeletal function, determined by the timed up and go test (the elderly person gets up from a chair with arms, walks three meters, turns round, walks back and sits down again). Taking more than 20 seconds indicates a high risk for falls.

- Stratification and potentially confounding variables; gender, age and other demographic data (social class, education level, marital status).

- Risk factors for falls: taking pre-disposing medication, health problems, toxic habits, physical exercise, living arrangements, sight or hearing difficulties, functional status (Katz index).

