- Treatment compliance. To determine this, the patient will bring the medication containers (empty or partially empty) to each visit. According to their degree of compliance (difference between number of tablets dispensed and number of tablets consumed) the patients will be classified as normal compliers (89-100%), hypercompliers (> 110%) or hypocompliers (< 80%). Compliance will also be evaluated by the Morisky-Green test.

- Serious adverse events or any other adverse event. An adverse event is considered as any untoward medical occurrence in any patient included in the study which does not necessarily have a causal relationship with the treatment. An adverse event can therefore be any unfavorable and unintended sign (including an abnormal laboratory finding), symptom, or disease temporally associated with the use of a medicinal product. Known adverse events of the calcium vitamin D combination at the proposed doses are: occasionally slight gastrointestinal alterations and the possibility of stimulating kidney stone formation in patients with impaired renal function.

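### Calcium and vitamin D are barred at entry but missing from the stated list of treatments not permitted during the study, and no other stated rule clearly covers or detects open use by a placebo patient

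*Protocol article*

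**What the plan says.** Protocol article, Study location and subjects: the exclusion criteria cover a need for calcium or vitamin D, and also "medical treatment that includes calcium or vitamin D". Thiazides, digitalis drugs, anticonvulsants, barbiturates, oral anticoagulants and hormone replacement therapy are excluded as well.

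Intervention: for the study period, "Concomitant treatment with thiazide diuretics, digitalis drugs, anticonvulsants or barbiturates will not be permitted". Four of the drug classes barred at entry are carried over. Calcium and vitamin D are not, and neither are oral anticoagulants or hormone replacement therapy. Study tablets are given from November to April over two years.

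Blinding and group assignment: eligibility is settled first. "After determining that the patients meet the inclusion criteria and do not meet the exclusion criteria, they will be randomized".

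Subject follow-up: "The following visits will be at 3, 6, 9, 12, 15, 18, 21 and 24 months". These visits collect efficacy and safety data, assess compliance and dispense medication. Violation of the protocol is one of the reasons for stopping treatment; starting or coming to need calcium or vitamin D is not listed.

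Definitions of the primary variables and measuring methods: compliance is the "difference between number of tablets dispensed and number of tablets consumed", supplemented by the Morisky-Green test. Calcidiol is a secondary variable, measured at baseline and at 6 and 18 months.

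Statistical analysis: the main analysis is by intention to treat. The per-protocol analysis excludes on selection criteria and on compliance with treatment.

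**The concern.** In a placebo-controlled trial of a supplement, the concomitant treatment that matters most is the supplement itself. A placebo patient who starts calcium or vitamin D openly becomes, in part, a treated patient. The entry criteria recognise this; the in-study list does not.

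The document itself makes open use plausible. Its Background describes calcium and vitamin D as central to treating osteoporosis, the trial performs densitometry and measures calcidiol, and recruitment is through primary care doctors. A patient or doctor could have reason to start a supplement during the two years.

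If that happens in the placebo arm, the risk reduction, the number needed to treat, the log-rank test and the Cox model are all pulled towards no effect. If use is not recorded, a null result cannot be told apart from a diluted one.

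**Working it through.** **Step 1. Does any stated rule cover open use by a placebo patient who was eligible at entry and takes every placebo tablet?**

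| Rule (section) | Clearly covers or detects it? |
|---|---|
| Exclusion criteria (Study location and subjects) | Applied before randomisation; not stated to continue afterwards |
| Treatments not permitted (Intervention) | Does not name calcium or vitamin D |
| Stopping for violation of the protocol (Subject follow-up) | Only if open use is a violation, which is not stated |
| Compliance (Definitions of the primary variables) | Concerns taking the study medication only; the patient counts as a normal complier |
| Per-protocol set (Statistical analysis) | Excludes on selection criteria and compliance; open use is not named |
| Calcidiol at 6 and 18 months | Could show vitamin D use, but not calcium alone or use begun after month 18; no rule acts on the result |

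None does so clearly.

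**Step 2. Reproduce the planned sample size.** Inputs from Sample size: 30% versus 20%, alpha 0.05 (taken as two-sided), power 80%. With p̄ = 0.25 and the pooled-variance normal approximation,

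n per arm = [1.96·√(2·0.25·0.75) + 0.8416·√(0.30·0.70 + 0.20·0.80)]² / 0.10² = 293.15.

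This agrees with the stated 293 per arm (294 if rounded up). Power at 293 per arm is 80.0%. The only allowance added is 20% for loss to follow-up; nothing is added for open use.

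**Step 3. Illustrate dilution.** Let c be the share of placebo patients with open use and f the fraction of the full effect that they get. Both are assumed, as the document gives neither. Open use in the treated arm is assumed to add nothing.

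- Placebo risk = 0.30 − 0.10·c·f, against 0.20 in the treated arm
- Absolute risk reduction (ARR) = 0.10·(1 − c·f); NNT = 1/ARR
- Power from the approximation in step 2, with 293 per arm

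| c | f = 1: ARR, NNT, power | f = 0.5: ARR, NNT, power |
|---|---|---|
| 0 | 10.0 points, 10.0, 80% | 10.0 points, 10.0, 80% |
| 5% | 9.5 points, 10.5, 76% | 9.75 points, 10.3, 78% |
| 10% | 9.0 points, 11.1, 72% | 9.5 points, 10.5, 76% |
| 20% | 8.0 points, 12.5, 62% | 9.0 points, 11.1, 72% |

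Full effect is an upper bound for patients who start partway through. Power stays at 75% or more up to c of about 6% (f = 1) or 13% (f = 0.5).

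**Step 4. Sensitivity to the time base.** The Abstract calls 30% an annual incidence, while follow-up is two years. If annual risks of 30% and 20% simply compound (an assumption that ignores the November to April dosing), the two-year risks are 1 − 0.70² = 51% and 1 − 0.80² = 36%. Power at 293 per arm is then about 96%. With f = 1 and placebo risk 0.51 − 0.15·c, it is 94%, 91% and 84% at c = 5%, 10% and 20%. The direction is the same, but power then stays above 80% at each of these uptakes.

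**The case against.** The strongest reply is that this is a condensed article. Full lists of prohibited medication, recording of concomitant medication and detailed deviation rules usually sit in the full protocol, the case report form or the SAP. The in-study sentence does not claim to be exhaustive, and it also omits oral anticoagulants and hormone replacement therapy, which looks like abbreviation. A broad reading of protocol violation, or of the selection criteria as continuing, would cover open use. Patients found at baseline to need calcium or vitamin D can be excluded before randomisation.

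Part of this stands. A reader might infer that the plan permits open use, or that an open user is certain to be counted as a clean per-protocol control. The text supports neither: it is silent, and the broad reading is open to the investigators. What does not fall away is that the article chose to print an in-study list, carried four entry exclusions over to it and left out the test substances. A site following that text has no clear instruction, and the broad reading is nowhere stated. Baseline screening does not deal with a need that arises later.

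A reader might also infer that the trial is underpowered. The documents do not support that: uptake and effect in users are assumed, and step 4 shows how much the answer depends on the time base.

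Finally, recording open use does not itself alter the intention-to-treat result. That is correct. Barring the use reduces dilution; recording it allows the result to be interpreted.

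**Conclusion.** The point holds as a gap between two stated lists: calcium and vitamin D are barred at entry, are absent from the treatments not permitted during the study, and are not clearly covered or detected by any other stated rule. The effect of open use in the placebo arm is dilution towards no difference. Its size cannot be estimated from the document. The figures of 76%, 72% and 62% are illustrations that rest on assumed uptake, full effect in users, no added effect in the treated arm and risks of 30% versus 20% over the whole follow-up. If open use is rare, the loss is small. The change is worth making because it is specific and cheap, not because a given loss of power has been shown.

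**What to change.** 1. Intervention: add *calcium or vitamin D other than the study medication* to the treatments not permitted during the 24 months.
2. Subject follow-up: at each of the eight existing 3-monthly visits, ask about such use and record it.
3. State that a patient who starts it or comes to need it may be treated, and stays in falls follow-up and in the intention-to-treat analysis in the randomised group.
4. Report open use by arm alongside the falls result.
5. If a per-protocol analysis excluding open users is wanted, label it a sensitivity analysis only. It is a post-randomisation exclusion, and those who start a supplement may differ in their risk of falls, so it can introduce bias.

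Cost: one clause in Intervention, short statements on follow-up and reporting, and one extra question per visit. Entry criteria and sample size do not change.
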